### Secondary endpoints

The secondary outcomes are:systolic and diastolic BP, for patients with diagnosis of hypertension;HbA1c and fasting plasma glucose, for patients with diagnosis of diabetes;quality of life, assessed by the the EuroQol five-dimension (EQ-5D) instrument [23,24];number of visits to the ED.

### Sample size

The sample size was estimated assuming a percentage of 50% nonadherence to the medication treatment in the control group [25]. To detect a 15% absolute increase in the medication adherence in the intervention group, a sample size of 190 participants will be needed in each group, considering an alpha error of 5% (bilateral), statistical power of 80% and 10% of losses to follow-up.

One of the researchers of the study will be responsible for quality control of the collected information. The participants will be randomly selected to answer a simplified questionnaire containing key issues by telephone. This control will be performed in 10% of the sample.

### Data analysis

The questionnaires will be entered into the database through processing by optical reader, using the Remark Office OMR® Software (version 8.0 Gravic, Inc., Malvern, PA) . All analyses will follow the intention-to-treat (ITT) principle. For the primary outcome, we will initially consider in the analysis patients with complete follow-up. A secondary analysis will be performed with data of all patients initially randomized, considering, as the worst plausible scenario, that 29% of the losses to follow-up, in both groups, are adherent. The worst plausible scenario was based on a previous observational study, conducted in 2012 in the same region, showing that 34.5% (95% confidence intervals (CI), 29% to 40%) of patients with hypertension assisted in basic health units are adherent according to the same instrument [26]. We will not use any imputation method for continuous outcomes, such as BP and blood glucose. For these outcomes, we will include only those participants who attended the follow-up visit.

Data will be presented as relative risk (RR) and mean difference (MD), with 95% CI. Categorical variables will be compared using the chi-square test; continuous variables will be compared using the Student *t-*test or the Mann–Whitney *U-*test. The analysis will be conducted in SPSS for Windows (version 19.0, Redmond, WA, USA) and Stata (version 10, College Station, TX, USA); the statistician will be blinded for the randomization status.

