## Methods/design

### Study design

This is a randomized controlled, single-center study, with blinding of outcome assessors. A pilot study with ten patients was previously conducted in order to test study logistics and data collection instruments. Participants will be recruited from a public ED at Restinga district in Porto Alegre, southern Brazil. Porto Alegre is the 10th largest city in Brazil, with 1.5 million inhabitants. Restinga is a low-income district of Porto Alegre, with approximately 100,000 people and a Human Development Index (HDI) of 0.700 to 0.799, whereas Porto Alegre HDI ranges from 0.700 to 0.977 [20]. This ED is the single reference emergency service of the southern region of Porto Alegre, with 8,000 visits monthly. Eligible participants will be randomized to either the intervention or the control group, and will complete a follow-up interview after a period of 2 months (Figure 1).

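### The plan declares every analysis intention-to-treat, but its lead primary analysis and its continuous-outcome analyses are complete-case, so the lead results are as-randomised completer effects and not ITT effects

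*Protocol article*

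**What the plan says.** All of this stands in one paragraph of the protocol article, under Data analysis. It opens with a general claim: "All analyses will follow the intention-to-treat (ITT) principle". The next sentence sets the lead analysis: "For the primary outcome, we will initially consider in the analysis patients with complete follow-up". The analysis that keeps everyone comes second: "A secondary analysis will be performed with data of all patients initially randomized", on the assumption "that 29% of the losses to follow-up, in both groups, are adherent". The plan presents 29% as its worst plausible scenario. The value is the lower confidence limit of the 34.5% adherence found in an earlier observational study of hypertensive patients in basic health units of the same region.

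For continuous outcomes there is no second analysis: "We will not use any imputation method for continuous outcomes, such as BP and blood glucose", and "For these outcomes, we will include only those participants who attended the follow-up visit". The planned comparison for them is a t-test or a Mann–Whitney test.

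Two other sections bear on the point. Sample size expects 10% loss to follow-up. Follow-up visit plans telephone contact and, where needed, home visits to limit losses.

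**The concern.** The paragraph itself separates patients with complete follow-up from all those randomised, and it puts the former first. A reader told that every analysis is ITT would take the headline relative risk as the effect in the 380 randomised. It is the effect in those who were followed up.

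That estimate is protected by randomisation only if loss is unrelated to outcome within each arm. The plan neither states nor defends this. Differential loss is possible: one arm has a 30-minute session with a pharmacist, while the other has printed material on top of usual care, and this difference in contact may affect who returns at 2 months. For BP, HbA1c and fasting glucose, the plan has no analysis that would show whether the missing patients matter.

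**Working it through.** **Inputs.** From Sample size: control adherence 50%, intervention 65% (a 15-point increase), two-sided alpha 5%, power 80%, 10% loss, 190 per arm. From Data analysis: 29% of losses adherent in both arms. Assumed here: completers show exactly 50% and 65%, and the unequal-loss splits in step 4.

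**1. The plan's own figure.** Two proportions, pooled variance, no continuity correction, mean proportion 0.575:

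n = [1.960 × √(2 × 0.575 × 0.425) + 0.842 × √(0.50 × 0.50 + 0.65 × 0.35)]² / 0.15² = 169.3, so 170 per arm.

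170 / 0.90 = 188.9, so 189, against the stated 190. The sample size reproduces. It is built on completers: 190 × 0.90 = 171 per arm, with power 80.4%. The lead analysis would leave out 19 per arm, or 38 of 380.

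**2. General formula.** With a fraction d of an arm lost, adherence p among completers and q among losses, adherence in all randomised is (1 − d) × p + d × q.

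**3. Equal 10% loss, q = 29% in both arms.**
- Control: 0.90 × 0.50 + 0.10 × 0.29 = 0.479
- Intervention: 0.90 × 0.65 + 0.10 × 0.29 = 0.614
- Difference 13.5 points, RR 0.614 / 0.479 = 1.28. Completers: 15.0 points, RR 0.65 / 0.50 = 1.30.
- Power with 190 per arm is about 75.5%, against 80.4% for completers.

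**4. Unequal loss, same 10% overall, q = 29% in both arms.** These splits are assumptions; the document gives no loss by arm.

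| Loss, intervention / control | Intervention | Control | All-randomised difference | RR |
|---|---|---|---|---|
| 15% / 5% | 0.85 × 0.65 + 0.15 × 0.29 = 0.596 | 0.95 × 0.50 + 0.05 × 0.29 = 0.4895 | 10.7 points | 1.22 |
| 5% / 15% | 0.95 × 0.65 + 0.05 × 0.29 = 0.632 | 0.85 × 0.50 + 0.15 × 0.29 = 0.4685 | 16.4 points | 1.35 |

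Completers give 15.0 points in both rows. In the first row the chi-square p-value is 0.037 in all randomised against 0.005 in completers. Completers overstate the scenario's effect in the first row and understate it in the second.

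**5. How far the secondary analysis reaches.** Setting q equal in both arms fixes the effect among losses at zero. The least favourable case for the contrast is that every lost control is adherent and no lost intervention patient is. At 10% loss per arm:
- Control: 0.90 × 0.50 + 0.10 × 1 = 0.55
- Intervention: 0.90 × 0.65 + 0.10 × 0 = 0.585
- Difference 3.5 points, RR 1.06.

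This is a bound, not a forecast. It shows that a low value shared by both arms does not stress the comparison between them.

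**6. Continuous outcomes.** No arithmetic is needed. ITT is claimed for all analyses, but these outcomes are limited to attenders and imputation is ruled out. No planned analysis of them includes all randomised patients.

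**The case against.** The best defence reads ITT as analysis in the assigned arm. On that reading, available outcomes analysed as randomised, plus an all-randomised sensitivity analysis, form a coherent plan, and the analysis set is disclosed in the very next sentence. For the primary outcome, the dispute is then over which of two pre-specified analyses leads. Telephone contact and home visits should also keep losses down, and at equal 10% loss the reported measure moves only from RR 1.30 to 1.28. All of this stands as mitigation. It does not turn a completer set into all randomised patients, and it gives BP and glucose no all-randomised analysis.

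Three stronger readings are tempting, and the document does not support them.

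- A reader might infer that the plan assumes informative missingness, because 29% lies below the 50% planned for controls. But 29% is offered as a pessimistic scenario. It comes from a general clinic population and not from dropouts, and the 50% rests on a different source. Comparing them says nothing about whether loss depends on adherence.
- A reader might say that the primary outcome is analysed in completers only. The secondary all-randomised analysis rules that out.
- A reader might extend the point to ED visits as an outcome that depends on attending follow-up. The abstract places outcome assessment at the 2-month visit, but no data source for ED visits is given, and the attenders-only sentence concerns continuous outcomes such as BP and blood glucose. An article may leave the source to the full protocol.

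**Conclusion.** The inconsistency holds on the text alone: the blanket ITT claim describes a property that the lead primary analysis and the continuous-outcome analyses do not have. They estimate complete-case effects by assigned arm.

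The numerical consequence is small if losses are equal and near 10%: 13.5 against 15.0 points. It is larger if losses differ by arm, 10.7 or 16.4 points under the splits shown, and its direction cannot be known in advance. Those figures rest on 50% and 65% in completers, 29% among losses, and loss splits chosen for illustration. A one-directional claim that completers inflate the effect would go too far. The sample size is not in question. The point should be corrected, and because the article reports recruitment as ongoing, this can be done before outcomes are analysed.

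**What to change.** **Primary outcome, preferred.** Make an all-randomised analysis primary, for example multiple imputation by arm using baseline adherence (listed among the questionnaires in the Figure 1 legend), the medication-count stratum and the other baseline variables. Keep the completer analysis, labelled complete-case. Add sensitivity analyses in which adherence among losses differs between arms, since one shared 29% does not test the contrast.

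**Primary outcome, minimum.** Keep the present order, label the lead analysis complete-case as randomised, and remove the statement that all analyses are ITT.

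**BP, HbA1c and fasting glucose.** Replace the unadjusted comparison with ANCOVA on the baseline value, which Baseline measures says is collected, and label it complete-case; or apply the same imputation.

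**Cost.** The change takes some analysis work, with no new data collection. Imputation assumes data are missing at random, so it would not recover the truth if losses depend on unobserved adherence; this is why the arm-specific sensitivity analyses are needed. Power may be slightly lower in the all-randomised analysis, about 75.5% against 80.4% under the 29% scenario with equal 10% loss. The minimum option costs only a change of wording.

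### The scenario labelled worst plausible (29% adherent among losses in both groups) is a low adherence level, not the case least favourable to the between-arm comparison

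*Protocol article*

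**What the plan says.** All of this is in the Protocol article, under Data analysis and Sample size.

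- Main analysis of the primary outcome: "For the primary outcome, we will initially consider in the analysis patients with complete follow-up".
- All-randomised analysis: "A secondary analysis will be performed with data of all patients initially randomized". The rule it sets for those who are lost reads: "considering, as the worst plausible scenario, that 29% of the losses to follow-up, in both groups, are adherent".
- Source of the 29%: an earlier local survey, described as "showing that 34.5% (95% confidence intervals (CI), 29% to 40%) of patients with hypertension assisted in basic health units are adherent". The 29% is the lower confidence limit of that estimate.
- Test: "Categorical variables will be compared using the chi-square test". Effects are reported as relative risks with 95% confidence intervals.
- Design rate for controls: "assuming a percentage of 50% nonadherence to the medication treatment in the control group".
- Effect sought: "To detect a 15% absolute increase in the medication adherence in the intervention group".
- Error rates and losses: "considering an alpha error of 5% (bilateral), statistical power of 80% and 10% of losses to follow-up". The planned size is 190 per arm.

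The article gives no scenario in which losses differ in adherence between the arms. It does not say how the assumed outcomes enter the variance.

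**The concern.** The result of interest is a comparison between arms. Missing outcomes threaten it mainly when those lost from one arm differ from those lost from the other, or when one arm loses more. A single value applied to both arms tests neither. What it does to the estimate depends on how many are lost from each arm: with equal losses it pulls the difference towards zero, and with enough extra losses in the control arm it pulls the control rate down further and enlarges the effect.

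Among the primary-outcome analyses in this article, this is the only one that includes everyone randomised, and the only stated robustness check. A reader told that the finding survived the worst plausible scenario would take more reassurance than the analysis can give. If the assumed outcomes are also counted as observed, the analysis gains apparent precision from patients nobody measured.

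**Working it through.** **Inputs.** From Sample size: 190 per arm, control adherence 50%, intervention adherence 65%, 10% losses, two-sided 5%, 80% power. From Data analysis: 29% among losses, and the interval 29% to 40%. Assumed here: loss rates that differ by arm, and any observed result other than 65% vs 50%.

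**The plan's own figure.** n per arm = [1.96 × √(2 × 0.575 × 0.425) + 0.842 × √(0.50 × 0.50 + 0.65 × 0.35)]² / 0.15² = 169.3, so 170. Then 170 / 0.90 = 188.9, so 189, against 190 stated. The sample size reproduces and is not in question.

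**Method.** Arm rate = observed rate × (1 − loss) + assumed rate × loss. The arms are then compared with 190 each by the pooled z-test (equivalent to chi-square).

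**Equal losses, 10% per arm, 65% vs 50%.**
- Control at 29%: 0.90 × 0.50 + 0.10 × 0.29 = 0.479.
- Intervention at 29%: 0.90 × 0.65 + 0.10 × 0.29 = 0.614.
- RD = 0.135. Pooled rate 0.5465; z = 0.135 / √(0.5465 × 0.4535 × 2/190) = 2.64; p = 0.008.

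| Adherence among losses (intervention / control) | RD, points | RR | p |
|---|---|---|---|
| Completers only | 15.0 | 1.30 | 0.005 |
| 29% / 29% (the plan) | 13.5 | 1.28 | 0.008 |
| 29% / 40% | 12.4 | 1.25 | 0.015 |
| 29% / 50% (control as completers) | 11.4 | 1.23 | 0.025 |
| 0% / 100% (extreme bound) | 3.5 | 1.06 | 0.49 |

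**Unequal losses, assumed 15% control and 5% intervention (10% overall).**
- Control at 29%: 0.85 × 0.50 + 0.15 × 0.29 = 0.4685.
- Intervention at 29%: 0.95 × 0.65 + 0.05 × 0.29 = 0.632.
- RD = 16.4 points; RR = 0.632 / 0.4685 = 1.35; z = 0.1635 / √(0.55025 × 0.44975 × 2/190) = 3.20; p = 0.0014. Completers: RD 15.0, RR 1.30, p = 0.005.
- With 29% / 40% instead, control is 0.485: RD 14.7, RR 1.303, p = 0.0039, so RR and p still look no worse than completers.
- With control losses at the completers' 50%, control is 0.500: RD 13.2, RR 1.26, below completers.

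**When the rule flatters.** RD rises when control loss × (0.50 − 0.29) exceeds intervention loss × (0.65 − 0.29), that is, when control loss exceeds 0.36 / 0.21 = 1.7 times intervention loss. RR rises when (0.65 − 0.36 × intervention loss) / (0.50 − 0.21 × control loss) exceeds 1.30, that is, when control loss exceeds 0.36 / 0.273 = 1.3 times intervention loss. With the imbalance reversed (5% control, 15% intervention), the rule works against the intervention: RD 10.7.

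**False positives.** In a simulation with no true effect (50% in both arms, losses at random, 29% entered as fixed values, 200,000 runs), false positives favouring the intervention were 4.7% with 15% control / 5% intervention losses and 7.1% with 20% / 5%, against a nominal 2.5%. With equal 10% losses the two-sided rate was 3.6% against 5%.

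**Precision.** With 171 completers per arm, the standard error (SE) of the RD is √(0.4775 / 171) = 0.0528. If the assumed outcomes are counted as observed, it is √((0.479 × 0.521 + 0.614 × 0.386) / 190) = 0.0506. At 20% losses per arm the pair is 0.0560 and 0.0509.

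**The case against.** The label can be read as describing the adherence level: 29% is the lower limit of a local estimate, applied openly to both groups. On that reading part of the complaint is about wording. This stands, but a check on a comparison has to be adverse to the comparison, and this one is not built to be.

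With equal losses the rule is conservative, and the article plans telephone contact, home visits and the same printed material for controls, all of which make a large imbalance less likely. That stands too. The 15% / 5% split is assumed; the article gives only 10%.

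A reader might infer that the protocol itself regards 29% for intervention and 40% for control as plausible. It does not. The only scenario it calls plausible is 29% in both groups, and the interval is sampling uncertainty around one rate in one population, not a range for how two arms' losses differ.

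A reader might also infer that the rule would pass a result that a fair check would overturn. At the design effect, 29% / 40% stays significant. A crossing can be found at an assumed 62% vs 50% (p=0.035 under the plan, 0.058 under 29% / 40%), but that result was picked: at 61% vs 50% the plan's own rule already takes p from 0.041 to 0.053.

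Finally, the loss of variance is inferred from the chi-square test and the all-randomised set. The article does not state it, and a separate analysis plan may handle it or add further sensitivity analyses.

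**Conclusion.** The point holds in a limited form and should be fixed. The 29% / 29% run is an equal-rate check, not a worst case for the comparison. With equal 10% losses at the design rates, it costs 1.5 points of RD, against 2.6 for 29% / 40% and 3.6 when control losses match control completers. With clearly more control losses than intervention losses, it improves on the completer result (RR 1.35 against 1.30 at 15% vs 5%); this depends on loss rates that are assumed here. The fall in SE from 0.0528 to 0.0506 depends on the assumed outcomes being entered as observed.

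A reader might go further and conclude that the primary result is biased or the trial underpowered. The documents do not support that: this is a secondary analysis, it leaves the completer result unchanged, and the sample size reproduces.

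**What to change.** Analysis and wording only, to be settled before outcomes are examined by arm (the article reports the trial as still recruiting):

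1. Rename the 29% / 29% run an equal-rate check and drop the worst-case label.
2. Make the main robustness check a tipping-point table over adherence among losses, varied separately by arm. Include cells in which control losses adhere at the control completers' rate or higher while intervention losses adhere at 29% or lower. Report where the conclusion changes and whether that pair is credible.
3. Show 29% / 40% as one illustrative cell only. Under 15% / 5% losses it still gives RR 1.303 and p=0.0039, so it does not cure the problem on its own.
4. Use multiple imputation, or another variance that reflects the missing data. This corrects the precision; it does not replace step 2, because it leaves the scenario's central estimate where it was.
5. Report losses by arm beside the table.

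The cost is a few hours of analysis and a revised paragraph. The robustness statement may become less favourable.

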**Figure 1 Fig1:**
[figure not shown]
**Flow diagram of the study design.** *Questionnaires: sociodemographic variables; comorbidities; medication adherence; physical activity; alcohol consumption. ^‡^For patients with hypertension. ^†^For patients with diabetes. ^††^Anthropometrical assessment: weight, height, waist and hip circumferences. BP = blood pressure; CPG = capillary plasma glucose; HbA1c = glycated hemoglobin.

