### Randomization and participants allocation

Following baseline data collection, eligible participants will be randomized to either the intervention or the control group in a 1:1 ratio, using a telephonic central for allocation concealment. The randomization sequence will be generated by using a computer program in blocks of four, six and eight. Randomization will be stratified according to the number of different medications in use (<5 or ≥ 5).

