### Primary endpoint

The primary outcome is the proportion of patients with high medication adherence at 2 months. Medication adherence will be assessed subjectively using two validated questionnaires in the Portuguese language: the Morisky-Green Test (MGT) and Brief Medication Questionnaire (BMQ) [21,22]. The MGT assesses both intentional and unintentional nonadherence and comprises four items. Responses for each item are scored one for ‘yes’ and zero for ‘no’ and are added together. A total score of zero represents good adherence and a score of one or more represents suboptimal adherence. The BMQ is composed of eleven questions, divided into three domains (regime, beliefs and memory).

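### The stated chi-square test for the primary outcome ignores the medication-count stratum used in randomisation; it is valid but slightly conservative and less efficient than an adjusted analysis

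*Protocol article*

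**What the plan says.** The Primary endpoint section defines a binary outcome: "The primary outcome is the proportion of patients with high medication adherence at 2 months". The Data analysis section then gives the test, "Categorical variables will be compared using the chi-square test", and says that effects will be presented as a relative risk or mean difference with 95% CI. It names no stratum and no covariate.

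The Randomization and participants allocation section states: "Randomization will be stratified according to the number of different medications in use", with the cut at fewer than five against five or more. Medication count is the only stratification factor.

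On baseline adherence the article is not explicit. The note to Figure 1 lists the questionnaires as "sociodemographic variables; comorbidities; medication adherence; physical activity; alcohol consumption". The Baseline measures section does not name adherence, although it covers the other four items in that list.

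**The concern.** Stratified allocation balances the arms on medication count, so between-stratum variation drops out of the treatment comparison. A plain chi-square still counts that variation in its standard error. If medication count predicts adherence, the interval is a little too wide and the test rejects a true null less often than 5%. Medication count is the one factor the investigators chose to balance, so it is natural to expect that they think it matters.

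Adherence before the intervention is a plausible predictor of adherence two months later. If it is recorded at enrolment, leaving it out of the primary analysis forgoes precision that costs no extra patients. At stake is efficiency, and agreement between the design and the analysis. Validity is not in question.

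**Working it through.** **Inputs from the protocol article (Sample size section).** Control adherence is 50% ("assuming a percentage of 50% nonadherence to the medication treatment in the control group"). The target is 65% ("To detect a 15% absolute increase in the medication adherence in the intervention group"). The error rates and losses are given as "considering an alpha error of 5% (bilateral), statistical power of 80% and 10% of losses to follow-up". The result is that "a sample size of 190 participants will be needed in each group".

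**Assumptions not in the article.** Phi, the within-arm correlation with 2-month adherence, is taken as 0 to 0.2 for the stratum and 0 to 0.5 for baseline adherence. The simulation also assumes two strata of equal size and 35% adherent at baseline.

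**Step 1: reproduce the sample size.** Pooled variance, no continuity correction:

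n = [1.960·√(2·0.575·0.425) + 0.842·√(0.50·0.50 + 0.65·0.35)]² / 0.15² = (1.370 + 0.582)² / 0.0225 ≈ 169.3, so 170 per arm.

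With 10% losses, 170/0.9 = 188.9, so 189, against 190 stated. The continuity-corrected version gives 183, then 204, and does not match. The trial was therefore sized for the plain, unadjusted comparison.

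**Step 2: power of the stated test.** Completers are 190 × 0.9 = 171 per arm.

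- SE under the null: √(0.48875/171) = 0.0535.
- SE under the alternative: √(0.4775/171) = 0.0528.
- Power: Φ[(0.15 − 1.960·0.0535)/0.0528] = Φ(0.856) = 80.4%.

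**Step 3: power with adjustment.** Multiply both SEs by √(1 − phi²). The number needed per arm for 80% power, with losses, is 170(1 − phi²)/0.9, rounded up.

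| phi | Power at 171 per arm | N per arm for 80% power |
|---|---|---|
| 0 | 80.4% | 189 |
| 0.1 | 80.8% | 187 |
| 0.2 | 82.0% | 182 |
| 0.3 | 84.0% | 172 |
| 0.4 | 86.7% | 159 |
| 0.5 | 90.2% | 142 |

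**Step 4: simulation.** 10,000 trials per setting, 342 completers, allocation balanced within stratum. MH is the Mantel-Haenszel test.

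| Stratum phi | Baseline phi | Type I, chi-square | Type I, MH by stratum | Power, chi-square | Power, MH by stratum | Power, MH by stratum and baseline |
|---|---|---|---|---|---|---|
| 0 | 0 | 4.9% | 4.9% | 80.9% | 80.7% | 80.2% |
| 0.1 | 0 | 4.4% | 4.8% | 80.5% | 80.7% | 80.3% |
| 0.2 | 0 | 4.1% | 5.1% | 81.3% | 82.2% | 81.8% |
| 0.1 | 0.2 | 4.4% | 4.8% | 80.9% | 81.0% | 81.9% |
| 0.1 | 0.3 | 4.6% | 5.1% | 80.0% | 80.3% | 83.4% |
| 0.1 | 0.4 | 4.6% | 5.0% | 81.2% | 81.5% | 87.4% |

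The stratum alone changes power by about 0 to 1 point. Adding baseline adherence gains about 1, 3.5 and 6 points at baseline phi 0.2, 0.3 and 0.4. The formula in Step 3 gives +1.6, +3.6 and +6.3. When neither variable is prognostic, the fuller adjustment costs 0.7 point (80.9% to 80.2%).

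**Step 5: cross-check of the type I error.** The large-sample value for the unadjusted test is 2·[1 − Φ(1.960/√(1 − phi²))], which is 4.9% at phi 0.1 and 4.5% at 0.2. The simulated 4.4% and 4.1% are a little lower. The simulation's standard error is √(0.05·0.95/10,000) = 0.2 point, and the discreteness of the counts also pulls the rate down. The stratum therefore accounts for only part of the shortfall from 5%.

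**The case against.** The strongest reply is that nothing here is wrong. The sample size was computed for the unadjusted test, and that test delivers its 80%. An unadjusted comparison after randomisation is unbiased, and its interval already allows for chance imbalance. The article is condensed, and an SAP that is not shown might add covariate adjustment. All of this stands, except that the last point does not remove the issue: the article does not leave the method open. It names a test, and that test does not follow the stratified design.

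A reader might infer more, and the document does not support it:

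- *That baseline adherence is certainly collected and then discarded.* The figure is not shown, and its note does not say which visit the questionnaires belong to. Adherence is also the 2-month outcome, so the note could refer to that visit. Since Baseline measures records the note's other four items, baseline collection is strongly implied, but it is not stated.
- *That a large gain, up to about 90% power, is being given up.* That needs a baseline correlation of 0.5, and the article gives no correlation. At 0.2 the gain is 1 to 2 points, and at zero it is nil.
- *That the trial is underpowered because of the test.* Power does fall to about 53% at an 11-point effect, the top of the range cited in the Background. That is a question about the assumed effect size.
- *That reporting only a relative risk conflicts with sizing on an absolute difference.* It does not. Adding the risk difference is a convenience, because readers could then compare the result directly with the 15-point target.

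**Conclusion.** The point holds as one of efficiency and of analysing as randomised. The stated primary test leaves out the stratification factor. It remains valid and meets its planned power, and it is at most slightly conservative.

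From the stratum alone the loss is about 0 to 1 power point for phi up to 0.2. Any larger gain comes from baseline adherence, and so depends on two things the article does not settle: whether it is measured at baseline, and how strongly it predicts the outcome. Over assumed phi of 0 to 0.4 that gain runs from nil to about 6 points. The downside, if neither variable is prognostic, is at most about 1 point. The simulated gains are for a Mantel-Haenszel test; a modified Poisson model was not simulated.

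**What to change.** 1. State that the primary analysis is adjusted for the medication-count stratum (<5 or ≥5). A Mantel-Haenszel relative risk, or a modified Poisson model with robust variance, would serve.
2. Reconcile the Figure 1 note with the Baseline measures section, and state whether adherence is assessed before randomisation.
3. If it is, add baseline adherence on the instrument that defines the primary outcome. The Primary endpoint section names two questionnaires and gives no rule for combining them, so the defining instrument must be fixed first. Give patients without a baseline value their own category.
4. Report the adjusted relative risk and the risk difference, each with a 95% CI.
5. Keep the chi-square as a supporting, unadjusted analysis.

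The stratum is known for every randomised patient, so items 1, 4 and 5 change only the analysis wording and need no new patients or data. The same is true of item 3 if baseline adherence is already recorded. If it is not, the adjustment stops at the stratum unless collection is added for patients still to be enrolled. The article reports that recruitment is under way, so the wording can be fixed before the outcome data are analysed.
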